## Abstract

**Background:**

In the era of highly active antiretroviral therapy HIV is now viewed as a chronic disease. Although people living with HIV are living longer lives, they are prone to a number of disabilities. Home-based rehabilitation has been shown to be an effective means of improving quality of life and function for people with a wide range of chronic diseases. There is a dearth of evidence, however, related to home-based rehabilitation interventions for people living with HIV, particularly in sub-Saharan Africa — the region with the highest global prevalence of HIV.

**Methods:**

A randomised controlled trial design will be employed. Adults living with HIV who have been on antiretroviral therapy for at least six months and with defined limited mobility will be randomly allocated to either an intervention group or the control group. Pre and post-intervention testing will be conducted at a public hospital in KwaZulu-Natal, South Africa in order to assess the participants’ quality of life, perceived level of disability, functional ability and endurance. Individuals randomly allocated to the intervention group will participate in a four-month home-based rehabilitation programme, conducted once a week in their homes. This programme will be implemented by community workers who will be trained and supervised by a qualified physiotherapist. The participants in the control group will continue with the standard clinic management offered to them. On completion of the intervention, all participants will be re-assessed using the same outcome measures. Analysis of results will be carried out on intention-to-treat basis in order to identify any changes between intervention and control groups.

**Discussion:**

The researchers aim to employ a novel task shifting approach to implement a needs-based home-based rehabilitation programme for people living with HIV in order to improve their quality of life and functional ability. It is hoped that this study will provide rehabilitation professionals and researchers with evidence that can be utilised to improve existing rehabilitation interventions for people living with HIV.

**Trial registration:**

South African National Clinical Trials Register: NHREC#4094 (Date of registration: 21 July 2015).

## Background

Globally, it is estimated that there are 35.3 million people living with HIV (PLHIV) with 25 million PLHIV in sub-Saharan Africa. An estimated 6.1 million people are currently living with HIV in South Africa [1], more than in any other single country in the world. Within South Africa itself, KwaZulu-Natal (KZN) has the highest HIV prevalence of all the country’s nine provinces, with 14.8 % of its inhabitants living with HIV. With improved treatment options for PLHIV, specifically the advent of highly active antiretroviral treatment (HAART), HIV is now viewed as a chronic disease rather than a terminal illness [2]. As an illustration of this, life expectancy in 2011 in KZN province was 11.3 years higher than in 2003, when the scale-up of HAART for PLHIV was in its infancy [1].

Although they are now living longer due to HAART, PLHIV are also more prone to a number of impairments and disabilities that may require rehabilitation. These disabilities may be permanent (such as blindness) or episodic in nature, with the extent of an individual’s impairments (and their experience of these impairments) fluctuating over time, depending on a number of inter-related factors [3]. A recent qualitative paper on the experiences of disability in PLHIV concludes that future HIV research needs to consider the new health care needs of PLHIV beyond a focus on clinical conditions and address the activity and participation restrictions that come with a life on HAART [4]. Rehabilitation services can help PLHIV address the life-related consequences of their medical condition [2] and can enhance their daily functioning via a number of strategies, including exercise [5].

Exercise and rehabilitation have been shown to be beneficial for PLHIV in a number of different settings [6, 7]. However, there is a great disparity in access to rehabilitation for PLHIV between developed and developing countries [8]. The current model prevalent in the South African public health system favours rehabilitation of patients in hospitals or clinics, despite evidence of the urgency to raise the profile of community-based rehabilitation (CBR) in South Africa at national, provincial and district levels [9]. This shortfall of widespread CBR provision is contrary to the South African Department of Health’s [10] vision of public health care delivery in South Africa moving towards a model that provides rehabilitation services in or near to patients’ homes. There is extensive evidence supporting the effectiveness of home-based rehabilitation (HBR) interventions for other chronic disease populations, including stroke [11–13] and coronary artery disease [14, 15]. However, there is a dearth of literature describing sub-Saharan African HBR interventions in general and no studies that have investigated HBR programmes designed specifically for PLHIV and disability in South Africa.

In the resource-poor community where this research is being conducted, PLHIV have identified a number of barriers to accessing the traditional institution-based physiotherapy rehabilitation available to them. These barriers include cost of rehabilitation, transport and accessibility issues [16]. This preliminary research has demonstrated the need for alternative evidence-based rehabilitation interventions for PLHIV in South Africa, particularly those living in resource-poor environments. The authors hypothesise that this HBR programme designed specifically for PLHIV and disability will have a positive effect on participants’ perceived disability, quality of life, functional mobility and functional capacity and will thus offer an effective alternative to institution-based rehabilitation for this patient population.

### Research question

What is the effect of a needs-based HBR intervention on PLHIVs’ perceived disability, quality of life, functional mobility and functional capacity?

### Aim

To determine the effect of a needs-based HBR intervention on PLHIVs’ perceived disability, quality of life, functional mobility and functional capacity.

### Objectives

To design a needs-based HBR intervention for adult PLHIV in a resource-poor setting using a task shifting approach.To determine the effects of the HBR intervention on participants’ perceived disability.To determine the effects of the HBR intervention on participants’ quality of life.To determine the effects of the HBR intervention on participants’ functional mobility.To determine the effects of the HBR intervention on participants’ functional capacity.

### Conceptual framework

This study uses the International Classification of Functioning, Disability and Health (ICF) as a guiding framework. The ICF [17] offers a useful framework for studying disability and health-related consequences of disease such as HIV [18]. This framework is based on three concepts: body function and structure, activity levels and participation. Changes in body function or structure (also named impairments) are understood to be problems with physiological functioning or anatomical (for example organs, limbs) structures of the body. Similarly, activity limitations are defined as difficulties in executing a task or action, such as walking or dressing. Finally, participation restrictions are problems relating to involvement in life situations [17]. Disability can be experienced at any of these levels and further influenced by inter-related environmental and personal factors (see Fig. 1). Thus, two individuals with the same impairment (for example, pain secondary to an HIV-related opportunistic infection) may experience markedly different activity limitations and participation restrictions, due to their respective socio-economic environments and specific personal characteristics. The authors of this study have utilised this framework in the design of this study in order to better reflect the overall lived experience of the participants who are exposed to the rehabilitation intervention.

**Fig. 1 Fig1:**
[figure not shown]
Graphic representation of the ICF framework

## Methods

### Study design

A randomised controlled trial (RCT) design will be used in this study in order to assess the effectiveness of a 16-week HBR intervention designed specifically for PLHIV and disability. The RCT is considered the highest level of evidence when attempting to establish the effectiveness of a chosen intervention [19].

### Study area

The study is located at a public hospital in the eThekwini district of the province of KwaZulu-Natal, South Africa. This hospital serves a population of 750,000 people in Mariannhill, which is an impoverished rural and peri-urban area on the outskirts of Durban. The hospital and its outlying clinics provide a service for more than 4,500 PLHIV [20]. The eThekwini district is one of the ten municipal districts in South Africa with the highest HIV prevalence, with an HIV prevalence of 38 % amongst expectant mothers [21]. While the assessment of patients pre- and post-intervention will be conducted on the hospital premises, the intervention itself will be conducted in, or near to, participants’ homes. These communities fall within the hospital catchment area, which is defined as including individuals living within the Inner and Outer West Operational Entities of the Durban Metropolitan Area, a large geographical area spanning approximately 40 kilometres [20].

### Study population

Participants for the proposed study will be recruited from the HIV-LIVE study, a large cohort study that included 1,043 PLHIV who receive HAART from clinics that fall under the study hospital described above. The HIV-LIVE study is an ongoing collaboration between the Health Economics in HIV/AIDS Research Division (HEARD) and the University of the Witwatersrand’s Department of Physiotherapy, which aims to determine the extent and impact of HIV-related disability on PLHIV in South Africa. It is a cohort study that employed a cross-sectional design and includes, as one of many assessment measures, the short form of the World Health Organisation Disability Assessment Schedule (WHODAS 2.0) assessment tool, a self-reported measure of disability [22].

### Study sample and recruitment

Individuals from the study population who meet the inclusion and exclusion criteria (see Table 1) will be contacted by telephone and invited to the study hospital. On their arrival, the study will be described in detail to each individual (in their home language—most of the study population speak isiZulu), each prospective participant will be given a study information sheet and they will be asked to sign an informed consent form, should they agree to participate in the study. Baseline blood pressure and heart rate measures will also be taken to ensure that each individual is fit to complete the pre-intervention testing. General questions about their current health will also be asked to ensure that individuals with acute illnesses are not exposed to further risk of testing. On agreeing to participate, all participants will continue to complete the four study outcome measures. Ethical approval for both the main HIV-LIVE study and this RCT has been given by the South African Department of Health, University of KwaZulu-Natal (UKZN) and the University of Witwatersrand.

**Table 1 Tab1:** Study inclusion and exclusion criteria

*Inclusion criteria*
Males and females living with HIV attending an outpatient HIV clinic of the study hospital
Individuals who have received HAART for six months or longer, specifically one of the national HAART regimens for adults, as outlined by the South African Department of Health.
Individuals over the age of 18
Individuals who scored for limitation in the mobility domain according to the WHODAS 2.0 (12 item version) assessment tool.
*Exclusion criteria*
Pregnant or breast-feeding women.
Any individual with an acute AIDS-defining opportunistic infection.
Any individual with a complete spinal cord injury with no possibility of being able to walk.
Unstable angina, recent myocardial infarction and elevated blood pressure (as per contraindications for the Six Minute Walk Test)

### Sample size

The sample size for this study has been calculated based on the group of participants from the HIV-LIVE cohort study who scored for limitation in the mobility-related questions (S1 and S7) of the WHODAS 2.0 (12 item version) tool. The effect size was chosen for these parameters. This was set at an alpha level 0.05 and allowed for a 40 % drop-out rate as indicated in previous studies (power of 80 %). A sample size of 80 participants is required, based on these parameters.

### Testing procedure

Five lay health workers, currently working in the study area for a non-governmental organisation, will conduct the pre-intervention testing, over a period of one week, at the study hospital. They will explain the nature and requirements of the study and provide each prospective participant with an additional study information sheet. Each individual will then be invited to participate in the study and, if they agree, asked to sign the consent form, in the full understanding that they be permitted to withdraw from the study at any point. Thereafter participants will undergo the pre-intervention testing. The four baseline outcome measures will each be conducted by a separate individual. The participants will be interviewed in their first language using a questionnaire including the short version of the World Health Organisation Quality of Life assessment tool (WHOQOL-HIV BREF) [23] and the short form of the World Health Organisation Disability Assessment Schedule (WHODAS 2.0). All interviews will be conducted in a private location, ensuring confidentiality and comfort for the participants. Following the interviews, the individual participant’s functional ability will be assessed using the Rivermead Mobility Index (RMI). After a five minute rest, the participant will then be invited to complete the Six Minute Walk Test (6MWT). Participants’ heart rate and blood pressure will be assessed before and after the test using an ambulatory wrist sphygmomanometer. Following the test, participants will be instructed to sit and rest for five minutes and offered water, after which time they will return home.

### Outcome measures

The WHOQOL-HIV BREF contains brief demographic questions, followed by 31 questions related to the individual’s perceived quality of life. The short form of the WHODAS 2.0 tool consists of 12 core questions assessing an individual’s perceived level of difficulty in carrying out certain day-to-day activities and participating in social, occupational and educational environments. The RMI is a 15-item assessment tool involving a combination of self-reported and directly observed measures of function, such as transferring from a bed to a chair and walking up and down four steps. Although initially designed to assess the functional ability of stroke patients, it is appropriate for populations with a range of physical disabilities [24]. The 6MWT is a test designed to assess distance walked over six minutes as a submaximal test of aerobic capacity/endurance [25]. The 6MWT will be performed, according to the test standards, indoors along a flat, hard surface in a hall on the study hospital’s premises. The walking course will be 20 metres in length, marked at every one metre. The turnaround points will be marked with cones. Absolute contraindications for the 6MWT include the following: unstable angina during the previous month and myocardial infarction during the previous month. Relative contraindications include a resting heart rate of more than 120, a systolic blood pressure of more than 180 mm Hg, and a diastolic blood pressure of more than 100 mm Hg [26]. Individuals who report absolute contraindications for the trial will not be considered for the trial. Individuals who present with any of the relative contraindications will have these measures taken twice more at 15-minute intervals, and if all of these readings are below the accepted limits, they will be able to continue with the trial. The four outcome measures employed in this study are described in more detail in Table 2.

**Table 2 Tab2:** Study outcome measures

Measure	Description
RMI	Assesses functional mobility in gait, balance and transfers. Consists of 14 self-reported items and one direct observation item, with items progressing in difficulty.
6MWT	This test measures the distance that a patient can quickly walk on a flat, hard surface in a period of 6 minutes. It evaluates the global and integrated responses of all the systems involved during exercise.
WHODAS 2.0 (12 item)	This is a self-reported assessment instrument for health and disability, directly linked to the ICF, used across all diseases. This 12-item version focuses primarily on activities of daily living and participation.
WHOQOL-HIV-BREF	This self-reported instrument, adapted for PLHIV, examines an individual’s perceptions of his/her quality of life across six domains: physical, psychological, independence, social, environment and spirituality.

### Randomisation and follow-up of participants

Following the pre-intervention assessments, participants will be randomly assigned to either the intervention group or a control group (standard care). Computerised randomisation and stratification (according to gender) will be employed in order to ensure homogeneity between intervention and control groups. This will be achieved using the randomise list [RAND()] function in the Microsoft Excel (2013) software package [27]. This will also satisfy allocation concealment, thus ensuring that the investigators will be unaware of to which group each participant will be allocated [28]. In the week immediately following the 16-week HBR intervention, participants from both intervention and control groups will return to the study hospital. The same four outcome measures will be assessed at this follow-up visit in order to ascertain the change from the pre-intervention measures.

### HBR intervention

The lead author (SC), a qualified physiotherapist, has conducted the training of four lay health workers who were selected from a pool of people who currently live in the area and volunteer as home-based carers for a non-governmental organisation in the study community. The training was conducted over a one-month period and was designed to equip these four individuals with the theoretical and practical skills to conduct the exercise and rehabilitation intervention at the homes of the participants randomised to the study intervention group. The HBR intervention will begin two weeks after the pre-intervention assessments to allow for the randomisation of participants and communication with each participant in the intervention group in order to set up a time for the first visit. The four health workers will work in pairs, with each pair being responsible for the rehabilitation of half of the participants in the intervention group. The justification for working in pairs is to ensure that participants will continue to be seen throughout the 16-week intervention, even if one of the health workers should be unavailable. Furthermore, it is often necessary for two individuals to assist a participant, particularly with mobility exercises such as learning to walk with crutches.

On the first home visit, SC will assess each participant and teach them strength and stretching exercises suitable for each individual. Upper limb and lower limb strength exercises will primarily be performed using MSD-Band [29] resistive bands (lightweight latex bands of varying resistance), which will be provided for each participant. Stretching exercises for the upper and lower limbs, trunk and neck will also be taught. Functional exercises, such as sitting to standing and bridging, will also be demonstrated where appropriate. All participants will also be encouraged, if able, to carry out a progressive walking programme over the 16-week period. Following this first visit, SC will fulfil a supervisory role, advising and helping the lay health workers if they have particular concerns or difficulty with any specific participant.

Following the first assessment week, when participants will begin their individualised HBR programmes, each participant will be seen in their own home once a week by their designated pair of health workers. Each appointment will be made by mobile phone call, and participants will be seen on a day and at a time convenient to them. While the majority of the participants in the intervention group are unemployed, home visits will also be scheduled for Saturdays to accommodate those participants who do work full-time. The stretching exercises will be performed at each visit, while the volume and resistance of the strengthening exercises will be progressively increased, as will the distance walked at each visit. Where possible, walking will be performed on the streets surrounding the participants’ homes, with each participant being accompanied by at least one health worker in order to ensure safety. Walking aids in the form of walking frames, elbow crutches and walking sticks will be provided to those participants who require them, following thorough assessment and instruction in their use by SC. Each participant will also be instructed on the specific home exercises they should do for the days between each weekly visit.

At each weekly visit, the health workers will complete a comprehensive entry into each participant’s individual diary, including information on the rehabilitation completed on that visit. The exercises done over the previous week, any equipment issued (such as resistive bands or walking aids) and any illness or problems that the participant may have had in the previous week will also be recorded. Should a participant not have been available to be seen at home on any given week, the reason for this will be noted in the diary and the above information will be elicited via telephone conversation and recorded in the diary. At the halfway mark of the intervention (after 8 weeks) the participants will be requested to select a date and time for their post-intervention assessment at the study hospital. They will be reminded of this follow-up appointment in the last (16th) week of the HBR intervention.

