### Control group

The participants randomised to the control group will receive the standard of care treatment offered by the specific clinic where they receive their HAART medication. They will be given a two-page information sheet on healthy living for PLHIV and encouraged to follow this advice. In the event that they are referred for rehabilitation by their clinic nurse or doctor, this will be conducted by a qualified physiotherapist at the study hospital’s physiotherapy department. Participants in the control group will receive a monthly phone call from one of the four lay health workers involved in the HBR intervention. These phone calls will serve to determine their health status and whether their contact/address details have changed. The phone call in the last month will also be utilised to set up a date and time for their post-intervention assessment at the study hospital. On completion of this study, should the HBR intervention be found to be effective, participants in the control group will be offered the opportunity to receive this intervention, at no cost to themselves.

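### Follow-up booking and reminders are set differently in the two arms, an avoidable risk of attrition that differs by arm

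*Protocol article*

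**What the plan says.** Under HBR intervention, the intervention arm is booked at mid-programme: "At the halfway mark of the intervention (after 8 weeks) the participants will be requested to select a date and time for their post-intervention assessment". The same paragraph adds the reminder: "They will be reminded of this follow-up appointment in the last (16th) week of the HBR intervention". These participants are also visited at home every week.

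Under Control group, contact is by telephone: "Participants in the control group will receive a monthly phone call from one of the four lay health workers involved in the HBR intervention". The purpose is stated: "These phone calls will serve to determine their health status and whether their contact/address details have changed". Booking is left to the final call: "The phone call in the last month will also be utilised to set up a date and time for their post-intervention assessment". The section describes no later reminder.

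Under Randomisation and follow-up of participants, both arms return to the hospital in the week after the 16-week programme, and the four outcomes are measured then. No other follow-up is described. Under Sample size, 80 participants are required after allowing for a 40% "drop-out rate as indicated in previous studies". That rate is given overall, not by arm.

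**The concern.** The visit that supplies all the outcome data is arranged by two procedures. One arm has an early booking plus a final-week prompt. The other has one booking call and, as far as the article says, nothing after it. The difference is not part of the treatment and could be removed without touching it.

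It matters here for three reasons. First, the loss allowed for is large, so a modest difference between arms involves many participants. Second, attendance is plausibly related to outcome: participants are selected for limited mobility, mobility and walking distance are outcomes, and the Background reports transport and accessibility as barriers to hospital-based rehabilitation in this community. Third, Data analysis explains intention to treat as keeping participants who did not adhere. That does not supply measurements for participants who never return. If loss differs by arm and is related to outcome, the comparison of those who attend is biased.

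**Working it through.** **The two procedures side by side**

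| Step | Intervention | Control |
|---|---|---|
| Routine contact | Weekly home visit | Monthly call |
| Booking | After 8 weeks | Last month's call |
| Reminder | Week 16 | None described |
| Visit | Week after the 16-week programme | Same |

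**Inputs from the article:** N = 80, alpha 0.05, power 80%, 40% drop-out allowed for.

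**Assumptions:** 1:1 allocation (40 per arm), a two-sided test, and 80 already including the drop-out. The retention splits and the correlations are also assumed.

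**The plan's own figure.** N = 80 cannot be reproduced forward because no effect size or SD is given. Working backwards, completers per arm = 40 × (1 − 0.40) = 24. The detectable effect is d = (1.96 + 0.84) × √(2/24) = 0.81 SD by the normal approximation, or 0.83 SD with the t distribution.

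**Bias under selection.** Take a standard normal outcome with no treatment effect, and retention p driven by a normal variable with correlation ρ to the outcome. The mean outcome among those retained is ρ × λ(p), where λ(p) = φ(a)/p and a = Φ⁻¹(1 − p). The spurious difference, control minus intervention, is ρ × [λ(control) − λ(intervention)]. Overall retention is held at 60%.

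- 65% v 55%: 0.720 − 0.570 = 0.150; times 0.3 to 0.5 gives 0.045 to 0.075 SD.
- 70% v 50%: 0.798 − 0.497 = 0.301; gives 0.09 to 0.15 SD.
- 75% v 45%: 0.880 − 0.424 = 0.456; gives 0.14 to 0.23 SD.
- 60% v 60%: the difference is 0, so there is no bias.

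At a correlation of 0.1 the 75% v 45% case gives only 0.05 SD.

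**Type I error.** With SE = √(1/n₁ + 1/n₂) on the completers and two-sided alpha 0.05, these biases raise the error rate to 5.3–5.8%, 6.1–8.1% and 7.4–11.9% for the three unequal splits.

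**Direction.** With positive ρ (those who stay do better) and fewer controls retained, the remaining controls are the more selected group and look better. The bias then runs against the intervention. Reversing either condition reverses the sign.

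**Power.** At d = 0.81, completers of 26 v 22, 28 v 20 and 30 v 18 give power of 79.7%, 78.9% and 77.4%, against 80.0% at 24 v 24. Even at 30 v 18 the effective size is 2/(1/30 + 1/18) = 22.5 per arm. The issue is bias, not power.

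**The case against.** A reader might infer that these procedures build unequal loss into the trial, or that retention must differ by arm. The documents do not support that. No arm-specific rate is given, and the 40% is a sample-size allowance taken from previous studies. Even the direction is open: sixteen weeks of home visits may themselves prompt withdrawals, and the Discussion recognises that attendance at the home could cause some participants harm or distress.

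A reader might also infer that controls get no reminder. The article does not say so. It is silent, and a condensed article can omit such a detail.

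Further points stand in the plan's favour:

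- The control booking call falls within about a month of the visit, so it does part of a reminder's work. A booking made 8 weeks ahead needs a prompt more.
- The control calls keep contact details current, transport and a food allowance are paid for both visits, and controls may be offered the programme afterwards.
- The larger imbalance, weekly visits against monthly calls, belongs to the intervention. Equal reminders would remove only part of any gap.
- ANCOVA is one of the named analyses. Adjusting for baseline would partly correct loss related to baseline status, and the calculation above ignores this.

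These points limit the claim to a risk of unknown size. They do not explain why booking time and reminder should differ. The article describes follow-up logistics for both arms in adjacent sections and in similar detail, and a final-week prompt appears for only one of them.

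**Conclusion.** The difference in procedure is stated in the text, and it creates an avoidable risk of attrition that differs by arm. Nothing in the documents shows that such attrition will occur, how large it would be, or which arm it would favour. Under assumed correlations of 0.3 to 0.5, the bias in a completers' comparison ranges from 0.045 SD (65% v 55% retention) to 0.23 SD (75% v 45%). That is about 6% to 28% of the back-solved 0.81 SD. The upper end needs a 30-point gap in retention, which nothing in the article supports as a result of booking differences alone. The case for change is that the risk is cheap to remove, not that serious harm has been shown.

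**What to change.** Use one procedure for both arms. Book every participant at the same time, for instance at week 8, using the home visit in the intervention arm and the second monthly call in the control arm. Then give every participant the same reminder call in week 16, counted from the same start date. If controls are in fact already reminded, say so in the Control group section and align the timing.

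The cost is about 40 extra short calls to controls (80/2, assuming 1:1 allocation) by the health workers who already phone them. If the intervention arm's reminder is currently given in person, a uniform call adds up to 40 more. The calls should stay with those workers, so that the blinded assessors have no contact that could reveal allocation. Sample size, outcomes and the intervention are unchanged. The imbalance in contact from weekly visits remains, so attendance should still be reported by arm.
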